### Patient Interview

After a center has had 5 patients with qualified emergency department visits, its team will begin to invite patients for interviews within 2 weeks of a qualified emergency department visit. The patient interview will assess the patient’s experiences using (or not using) the E-IPP, what was helpful and challenging about using the E-IPP, if pain treatment has changed (or not changed) because of the E-IPP, patient satisfaction with the E-IPP, proposed recommendations to improve the E-IPP, intent to use the E-IPP in the future, and additional questions on implementation strategies such as the wallet card. The research team will use purposeful sampling for qualitative data collection [38], based on matched patient and provider survey responses and implementation outcomes of the IPPs.

### Provider Baseline and Follow-up Survey

Each participating site will administer a brief provider baseline survey at the time of provider enrollment that will assess provider-perceived quality of emergency department pain treatment and provider’s self-efficacy to manage acute pain episodes for patients with sickle cell disease. Within 96 hours of a qualified emergency department visit, the research team will send a follow-up survey via email to the enrolled provider who ordered the first analgesic. The provider follow-up survey will assess use of E-IPP, ease of E-IPP use, E-IPP adherence, perceived quality of emergency department pain treatment, satisfaction with the E-IPP, and intent to use the E-IPP in the future.

### Provider Interview

After a center has had 5 patients with qualified emergency department visits, the team will begin to invite providers who ordered the first analgesic for interviews within 2 weeks of a qualified emergency department visit. The provider interview will assess provider’s experiences using (or not using) the E-IPPs, what was helpful and challenging about using the E-IPPs, proposed recommendations to improve the E-IPPs, intent to use the E-IPP in the future, and additional questions on implementation strategies. The research team will use purposeful sampling for qualitative data collection [38], based on matched patient and provider survey responses and implementation outcomes of the E-IPPs.

### Emergency Department Administrator Interview

At the end of the implementation period, each site team will invite emergency department administrators to a postimplementation interview that will assess barriers and facilitators to intervention implementation, emergency department administrator’s experiences implementing and using the E-IPP, and emergency department administrator’s intent to continue using the E-IPP in the future.

### Tracking and Reporting Implementation Strategies

A parallel study has been funded to capture the planned and actual implementation strategies employed by each site [39]. Semistructured interviews with 3 stakeholders from each site before participant recruitment and at the end of the intervention, as well as quantitative surveys at the midpoint of project implementation, will capture the barriers and facilitators of the strategies planned and whether there have been any adaptations made. Questions have been informed by the implementation and maintenance domains of the RE-AIM framework.

### Statistical Analysis Power and Sample Size

The study plans to have an analytical sample size of 160 patient participants, 20 for each site, for its primary outcome analysis. Each site is expected to enroll approximately 40 participants to reach the analytical sample size.

Sample size was calculated for the primary outcome, patient satisfaction with emergency department pain treatment through their perceived quality of emergency department pain treatment. For the power calculations, we used results from the Sickle Cell Disease Implementation Consortium needs assessment [17, 23], which used similar measurements to assess patient satisfaction with emergency department pain treatment. We assumed that the correlations between responses would not change and conducted a simulation to determine statistical power to detect a treatment difference of half a standard deviation. The sample estimation model has several assumptions: the intervention effect will vary across sites with the standard deviation for the random intervention effect set at 0.447; within-site correlation (commonly referred to as intercluster correlation) of baseline measurements, calculated as the ratio of site-level variance over the total variance, is set at 0.10; and within-participant correlation, calculated as the ratio of individual-level variance over total individual variance, is set at 0.50, reflecting the expectation that the preintervention composite score is predictive of the postintervention score.

Based on the Sickle Cell Disease Implementation Consortium registry data, we estimated that at least 50% of the study patient participants will have at least 1 qualified emergency department visit during the study period and that approximately 20% of the participants will be lost to follow-up and provide no posttest data. The total number of patients a site will recruit is approximately 40. The results indicate that the study will have >90% power to reject the null hypothesis when the intervention results in an average improvement in patient-perceived quality of emergency department care of 0.5 standard deviations under the assumed conditions.

### Data Analysis

#### Primary Outcome

The primary outcome is patient satisfaction with emergency department pain treatment through their perceived quality of emergency department pain treatment (Multimedia Appendix 2). This is measured with a composite of 3 questions developed based on the Adult Sickle Cell Quality of Life Measure Quality of Care measure [6]. The impact of the intervention on the primary outcome will be estimated using a linear mixed model. A 3-level model with random effects for site, participants nested within site, and site-to-site variation in the treatment effect and a fixed effect for treatment response will be specified to assess the impact of the intervention. The primary analysis will be based on the preintervention composite score and the score at 1 emergency department visit per participant, using the first visit for those with more than one. The model can accommodate multiple visits per participant by adding a covariance matrix to account for repeated observations.

#### Other Outcomes

The secondary outcomes of hospital admission rate (a count outcome, as multiple hospital admissions are possible), 7-day emergency department vaso-occlusive episode revisit (a dichotomous outcome), and time to first dose, and other provider-level outcomes will be analyzed with generalized linear mixed models, where the outcome will be specified as a Poisson or binomial variable with a logit function as needed by the data type of outcome. The generalized linear mixed models would follow the same format as the linear mixed model with fixed effects for time, intervention, and covariates and random effects for participants within sites. The secondary outcome of satisfaction with IPP, measured with a single Likert scale question for both patient and provider, will be analyzed as a continuous outcome with a linear mixed model as detailed above for the primary outcome. In all cases, the analysis will estimate an intervention effect that will compare the secondary outcome at baseline to after the intervention is delivered. Power calculations indicate that the study sample will be too small to detect statistically significant differences in these noncontiguous variables, but estimates will be provided to inform future research.

The analysis of the quantitative readiness assessment result and the reach, adoption, implementation, and maintenance outcomes will be descriptive. As a preliminary attempt, at the end of the intervention, the results of the readiness assessment will inform our interpretation of the implementation and effectiveness outcomes. Sites with a lower level of readiness may face challenges during implementation, which will affect their implementation outcome and intervention effectiveness.

For qualitative interviews, the workgroup members will develop a codebook informed by the RE-AIM framework for data analysis. Using a deductive approach, the codebook will include an initial list of codes to be used in the analysis and definitions or operationalized examples for each code. Analysts will revise the codebook as necessary to hone definitions to increase consistency in coding across the research teams. Data will be compiled into different stakeholder groups by themes and analyzed across the study sites.

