**Figure 4 figure4:**
[figure not shown]
Study flow chart. ED: emergency department; EHR: electronic health record; VOE: vaso-occlusive episode.

Given that sickle cell disease is a rare disease and most patients with sickle cell disease do not have frequent emergency department visits per year, the preimplementation and postimplementation design without control groups is the most feasible study design. Sites will overenroll participants to ensure that enough participants will have a qualified emergency department visit during the implementation period. Additionally, it took a few months to 2 years for sites to work with their local informatics teams to make the E-IPPs available to emergency department providers and patients; therefore, a waitlist-control or stepped-wedged design is not feasible given the study timeline.

The study rollout will allow for emergency department provider training of the E-IPP, development and implementation of the E-IPPs, and evaluation postimplementation. Because of the COVID-19 pandemic, sites have adjusted to the rollout timeline. Two sites began the project in September 2020. The active implementation period is 12 months from the first day of patient enrollment, and the overall implementation phase will be 18 months.

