#### Provider Recruitment

All emergency department providers will be able to access the E-IPPs and will receive training on the protocol at staff meetings, resident conferences, or through emails. All emergency department providers will be invited to complete a baseline survey at enrollment with an information sheet introducing the study. If an enrolled patient participant has a qualified emergency department visit and the corresponding emergency department provider has not received training or completed the baseline survey, the study team will send a provider follow-up survey to the provider at enrollment with an information sheet introducing the study.

A qualified emergency department visit is defined as (1) a visit for an enrolled patient to a participating emergency department, the reason for the visit is a vaso-occlusive episode, and the patient has an E-IPP at the time of the emergency department visit; and (2) the patient’s first emergency department vaso-occlusive episode visit of the month, after enrollment, within the 12 month study period for that patient.

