### EHR Data Retrieval

Each participating site will perform EHR data retrieval for enrolled patients’ past 12 months ED visits and qualified ED visits to collect: hospital admission rate; 7- and 30-day emergency department revisit rate; 7- and 30-day hospital readmission rate; time to first dose of analgesic agent; and administered analgesic agent, dose, and route. At the end of the project, the site will also retrieve the following from the EHR: number of E-IPPs written and time of writing or updating, number of new E-IPPs available in the EHR and time of becoming available, and number of new patients at each site who are being offered access to their pain plan in the EHR after study enrollment targets are met. Data retrieval will follow a manual of procedures created by the workgroup to reduce bias [36,37].

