## Results

At the time of submission, this study was approved by the institutional review board of Duke University (IRB Pro 000073506), Icahn School of Medicine at Mount Sinai (IRB 20-04302), Medical University of South Carolina (IRB Pro 00097830), Washington University School of Medicine (IRB 202006209), University of California San Francisco (IRB 20-30981), University of Illinois Chicago (IRB 2016-02998). The full protocol and study manual of procedures are available from the corresponding author upon request. The study is registered (NCT04584528) and enrolling participants. Sites that did not have IPPs for all patients are working with the sickle cell disease providers to build the plans with patients during clinic visits. Because of the COVID-19 outbreak, sites have changed the planned recruitment timeline and will continue enrolling until the target is reached.

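### Hospital admissions are modelled as a count with no exposure term, although post-implementation observation time can fall short of the 12-month baseline but never exceed it, and the two periods count different visits

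*Protocol article*

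**What the plan says.** All references are to the protocol article.

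- **Other Outcomes** introduces the outcome as "hospital admission rate (a count outcome, as multiple hospital admissions are possible"). On distribution and link it says "the outcome will be specified as a Poisson or binomial variable with a logit function as needed by the data type of outcome". The models are to be fitted "with fixed effects for time, intervention, and covariates and random effects for participants within sites". The estimate compares baseline with the period after the intervention is delivered. The section concedes that power is too low for these outcomes and offers the estimates as input to later research.
- **EHR Data Retrieval** takes admissions and the other record-based outcomes from enrolled patients' "past 12 months ED visits and qualified ED visits".
- **Provider Recruitment** defines a qualified visit. It must be for a vaso-occlusive episode at a participating department, and one condition is that "the patient has an E-IPP at the time of the emergency department visit". It must also be the patient's first such visit of the month, after enrolment, within a 12-month study period for that patient.
- **Study Design** sets the calendar: "The active implementation period is 12 months from the first day of patient enrollment, and the overall implementation phase will be 18 months". The abstract instead gives 18 months for the active period.
- **Results** says that sites lacking plans for all patients are still building them, and that sites "will continue enrolling until the target is reached".

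**The concern.** A count is comparable between two periods only if the periods are equally long and the same events are counted in each. Here the baseline is a full 12 months for everyone. After enrolment, 12 months is the maximum, and three things can shorten it:

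- the plan goes live some time after enrolment, because earlier visits do not qualify;
- the patient is lost to follow-up;
- the patient enrols late and data retrieval ends with the 18-month phase.

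Nothing lengthens it, so the time errors cannot cancel: they either vanish or push the estimate towards fewer admissions.

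The visit sets differ as well. All emergency department visits count before; only the first qualifying visit of each month counts after. That also lowers the post count.

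There is no control group, so a ratio below 1 would naturally be read as benefit. Because the estimate is meant to inform future work, bias in the point estimate matters more here than significance does. Sites that enrol or build plans at different speeds would also appear to differ in effect.

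**Working it through.** The article gives no admission rate or expected ratio, so there is no published figure to reproduce.

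**Observation time.** Inputs from the article: 12 months before, at most 12 months after, an 18-month overall phase. Assumptions: a constant admission rate and no intervention effect; enrolment time *e* uniform over *A* months; data closing at month 18; a delay of *d* months from enrolment to a live plan. Then

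post months = min(*e* + 12, 18) − *e* − *d*,

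and for *A* of at least 6 the mean is 12 − (*A* − 6)²/(2*A*) − *d*. The expected post/pre count ratio is that mean divided by 12.

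| Enrolment *A* (months) | Delay *d* (months) | Mean post months | Ratio with no effect |
|---|---|---|---|
| 6 | 0 | 12.0 | 1.00 |
| 9 | 0 | 12 − 9/18 = 11.5 | 0.96 |
| 12 | 0 | 12 − 36/24 = 10.5 | 0.875 |
| 12 | 1 | 9.5 | 0.79 |
| 12 | 2 | 8.5 | 0.71 |
| 12 | 3 | 7.5 | 0.63 |
| 15 | 0 | 12 − 81/30 = 9.3 | 0.78 |
| 18 | 0 | 12 − 144/36 = 8.0 | 0.67 |

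Check of the third row: half the patients enrol by month 6 and keep 12 months; the other half average (12 + 6)/2 = 9; the mean is 10.5.

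**Simulation with no effect.** 160 patients, between-patient variation in rate (gamma, variance 1, assumed), and 1 to 3 admissions a year (assumed). Without person-time, a nominal 5% test rejects in 22% to 52% of runs where the ratio is 0.875, and in 50% to 90% where it is 0.79. With person-time, the ratio returns to about 1.00 and rejection to about 4% to 6%. This simulation captures the same visits in both periods, which the plan does not.

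**Visit definition.** Suppose the windows are equal at 12 months, visits occur at a constant rate of *v* per year, and admission is equally likely at each visit. The share of visits kept by a first-of-month rule is 12(1 − exp(−*v*/12))/*v*. For *v* = 1, 3, 6 and 12 this is 0.96, 0.885, 0.79 and 0.63. A person-time offset leaves this loss untouched, because the time is observed but the visits are not counted.

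**The case against.** The strongest reply is that the article is silent rather than wrong. It calls the outcome a rate, leaves covariates open, and condenses a full protocol that may specify an offset. The stated per-patient windows are also 12 months against 12. Nothing says that a patient's follow-up stops at month 18, and 6 months of enrolment followed by 12 months each fits the 18-month phase exactly. The delays of 1 to 3 months have no source. The teach-back at orientation, in which patients show staff how they reach their plan, and the site requirement for an accessible E-IPP both suggest plans that are live at or near enrolment.

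Much of this stands. A reader might infer that the model must show a fall, or that the plan rules out person-time. The documents support neither: the time artefact can be zero, and no exclusion is stated. A reader might also infer that an offset alone would restore a ratio of 1.00. It would not, because the visit sets differ.

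What remains is that the article does more than omit a detail. It converts a rate to a count, lists the model terms, and names only a logit function, whereas a Poisson rate model with an offset needs a log link. The reason given for using a count, that several admissions are possible, fits a per-patient total. If admissions per visit were meant, the exposure would be visits rather than months, and the article should say so.

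**Conclusion.** The point holds in a limited form. As described, the model has no term for unequal observation time, and any such inequality runs only towards a spurious fall. Its size cannot be fixed from the article. With uniform enrolment it ranges from none (enrolment within 6 months, plans live) to 12.5% (12-month enrolment, data closing at month 18), and to about 21% to 37% with an added delay of 1 to 3 months. The month-18 cut-off, the uniform enrolment and the delays are assumptions. Loss to follow-up would add to the shortfall and is not quantified here.

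The difference in visit definition does not depend on those assumptions. It is explicit in the text, and only its size depends on visit frequency. The consequence is modest: this is a secondary outcome, reported for estimation, and the primary outcome is unaffected.

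**What to change.** In Other Outcomes:

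1. State that the outcome is admissions per patient per unit time. Fit the count model with a log link and an offset of log observed months. Pre is 12 months. Post runs from the later of enrolment and E-IPP availability to the earliest of 12 months after enrolment, loss to follow-up and the end of data retrieval.
2. Use one visit definition in both periods: either all vaso-occlusive visits, or the first of each month. Applying the first-of-month rule to the baseline needs no further visits retrieved but discards some baseline data. Using all visits after enrolment means retrieving more than the qualified ones.
3. State when retrieval ends, and reconcile the 12-month and 18-month active periods.

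The cost is small: one derived variable, a few sentences and a little analysis work. Patients with short post time receive slightly less weight. EHR Data Retrieval already lists when new E-IPPs become available, but does not say that these dates are linked to individual patients, and it does not list dates of loss to follow-up. Both need confirming before the offset can be built.

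### Only Poisson or binomial models are named for time to first dose, a continuous duration that neither fits; a Poisson interval for it would depend on the time unit

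*Protocol article*

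**What the plan says.** The EHR Data Retrieval section lists "time to first dose of analgesic agent" among the items taken from the record. No unit is stated.

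The Other Outcomes section names hospital admission, labelled a count, and 7-day revisit, labelled dichotomous. It continues "and time to first dose, and other provider-level outcomes will be analyzed with generalized linear mixed models", with no data type given for the time. For all of these, "the outcome will be specified as a Poisson or binomial variable with a logit function as needed by the data type of outcome".

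The section says these models share the format of the primary model, and then lists "fixed effects for time, intervention, and covariates and random effects for participants within sites". The Primary Outcome section gives that primary model "random effects for site, participants nested within site, and site-to-site variation in the treatment effect". The only secondary outcome that "will be analyzed as a continuous outcome with a linear mixed model" is satisfaction with the pain plan.

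On the role of these results, the section states: "the study sample will be too small to detect statistically significant differences in these noncontiguous variables, but estimates will be provided to inform future research".

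**The concern.** The qualifier about data type chooses between two named families. Poisson suits counts and binomial suits yes/no outcomes; an elapsed time is neither. No gamma, lognormal, log-transformed or time-to-event model is named for it, and no threshold is stated. This is therefore more than a detail left to an analysis plan: the article fixes a set of families that contains no suitable one for this outcome.

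A Poisson model ties the variance to the mean. A count has a natural unit of one, but a duration does not, so recording the same visits in minutes or in hours changes how precise the model claims to be. These outcomes are meant to supply estimates for later studies, so the interval is a main part of what is delivered.

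**Working it through.** The article states no figure for time to first dose, so there is nothing of its own to reproduce.

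**Inputs**
- Design: "analytical sample size of 160 patient participants, 20 for each site" (Statistical Analysis Power and Sample Size), used as 160 pairs of one pre and one post value.
- Correlation between a participant's two log times: 0.5. The article sets this value for the primary composite; borrowing it here is an assumption.
- Mean of 60 to 120 minutes and coefficient of variation (CV) of 0.5 to 1.0: assumptions, since the article gives neither.
- Random effects: participants within sites, as listed in Other Outcomes.

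**Poisson model**

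With a participant intercept and one value in each period:
- estimated log ratio = log(sum post / sum pre), in which the unit cancels;
- model SE = sqrt(1/sum pre + 1/sum post), in which it does not.

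Example with mean 90 minutes and no true effect:
- minutes: each sum is 160 × 90 = 14,400, so SE = sqrt(2/14,400) = 0.0118;
- hours: each sum is 160 × 1.5 = 240, so SE = sqrt(2/240) = 0.0913;
- ratio of the two = sqrt(60) = 7.75, whatever the mean or CV.

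**True standard error**

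True SE ≈ sqrt(2 × CV² × (1 − r)/160), with r the pre/post correlation of the times themselves. For lognormal times with log-scale correlation 0.5, r = (sqrt(1 + CV²) − 1)/CV². At CV 0.75, r = 0.25/0.5625 = 0.444, and the true SE = sqrt(2 × 0.5625 × 0.556/160) = 0.063. So true/model is about 5.3 in minutes and 0.69 in hours. The number of pairs cancels from this ratio.

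**Simulation**

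4,000 runs per setting, 8 sites × 20 participants, lognormal times, no true effect and no true site variation in effect; minutes rounded, hours not. The table shows the two extremes and the centre of the nine mean/CV combinations. The last two columns give how often a nominal 95% interval misses the true ratio of 1.

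| Mean, CV | True SE | Model SE, min (true/model) | Model SE, h (true/model) | Misses, min | Misses, h |
|---|---|---|---|---|---|
| 60 min, 0.5 | 0.0408 | 0.0144 (2.82) | 0.1119 (0.36) | 50% | 0% |
| 90 min, 0.75 | 0.0626 | 0.0118 (5.31) | 0.0914 (0.69) | 71% | 0.4% |
| 120 min, 1.0 | 0.0833 | 0.0102 (8.14) | 0.0793 (1.05) | 80% | 6.8% |

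With correlation 0 (mean 90, CV 0.75), true/model is 7.16 in minutes and 0.92 in hours.

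**Adding a random site-by-treatment slope**

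This was approximated, for minutes only, by random-effects pooling of the eight site log ratios. At mean 90 and CV 0.75 the model SE becomes 0.059 against a true 0.063, and the interval misses in about 9% of runs. Over all nine combinations the miss rate is 8.6% to 10.2%, using a normal critical value on 8 sites.

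**Model on log time**

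SE = sqrt(2 × ln(1 + CV²) × (1 − 0.5)/160) = 0.037, 0.053 and 0.066 at CV 0.5, 0.75 and 1.0, the same in minutes or hours. As in the simulation, this assumes no site variation in effect.

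**The case against.** **The site slope.** The section says these models follow the format of the primary model, which has a random treatment effect by site. If that term carries over, it absorbs the extra-Poisson noise and the minutes interval is nearly right. This stands as a real limit on the size of the problem. It does not settle the matter, because the list given for these models names only participants within sites. A random slope also only adds variance, so it cannot narrow an interval that is too wide, as it mostly is in hours.

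**A binary version.** If the time was meant to be cut at a threshold, a binomial model is valid and the unit no longer matters. The section's description of these outcomes as noncontiguous, apparently meaning not continuous, makes that intent possible. But no cut-off is stated, and cutting discards information.

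**The figures are assumed.** The mean, CV and unit are not in the article. Only the factor of 7.75 between units is free of these assumptions.

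**Weight.** This is one secondary outcome in a condensed article, and the article says that these comparisons are underpowered. The miss rates therefore matter as interval coverage, not as errors of a test that the study relies on.

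A reader might also infer that the plan puts a logit link on the Poisson admission count. The text does not support that: the logit attaches naturally to the binomial option, and leaving the log link unnamed is an ordinary omission.

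**Conclusion.** The point holds. The article names only Poisson or binomial for a positive continuous duration, and neither fits without a cut-off that is not given. If Poisson is used, the estimate survives but its standard error depends on the unit by a factor of 7.75. Under the assumed means, CVs and correlation, and the listed random effects alone, it is about 2.8 to 8.1 times too small in minutes, and from about 2.8 times too large to about right in hours.

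Three stronger inferences are not supported. The interval is not bound to be several times too narrow: that needs minutes and no site slope. The estimated ratio itself does not shift materially with the unit. The primary outcome, which has its own linear mixed model, is not affected. The harm is limited to the interval of one secondary, estimation-only result; the correction should still be made because it is simple.

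**What to change.** In Other Outcomes, take time to first dose out of the Poisson/binomial sentence. Analyse log(time) with the same linear mixed model as the primary outcome, including the site-level treatment slope, and report the post/pre ratio of geometric means with its interval. A gamma model with log link and the same random effects, reporting a ratio of means, would also serve. Keep Poisson for the admission count and binomial for the dichotomous revisit outcome. If a binary version of the time was intended, say so and state its cut-off in advance.

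The cost is a change of wording in the analysis section. It needs no new data and places no burden on patients or sites.
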